Overall quality of life indicators: The CGI and the Q-LES-QSF will be used for assessment. The CGI will focus on the participants’ overall assessment of their clinical impressions and treatment satisfaction. The Q-LES-QSF will evaluate participants’ happiness and satisfaction across different aspects of daily life.

Data Entry and Management

In this study, an electronic data capture (EDC) database will be established, and all the data will be collected in the form of electronic case report forms (eCRFs). EDC will be employed in this multicenter trial to ensure data consistency across study sites and enhance traceability, both of which are critical for maintaining compliance with Good Clinical Practice (GCP) guidelines (ICH-GCP E6(R3), Sections 2.10 & 5.5) [22]. EDC systems minimize transcription errors, enable real-time data validation, and provide an audit trail for regulatory inspections, thereby improving overall data integrity and reliability. Within this trial, the investigators will meticulously record various information, including informed consent, enrolment time, use of investigational drugs, vital signs, relevant physical examinations, laboratory tests, scale assessments, concomitant medications, and adverse events. The clinical research coordinators (CRCs) will be responsible for accurately, promptly, completely, and consistently entering the raw data into the system, ensuring traceability for each data point.

The data manager will need to be trained in data management-related SOPs and familiarized with data management-related regulations and guidelines before participating in project work. Data management will include data validation and cleaning. The purpose of data validation will be to ensure data accuracy and completeness. The data manager will formulate a detailed and complete data validation plan (DVP) on the basis of the protocol and CRF. These plans will include automated logic checks, SAS program checks, manual checks by medical/data administrators, and source data verification (SDV). The clinical research associate will be responsible for the SDV, which will validate the consistency of the eCRF data with the source data by reviewing the original visit records. For laboratory and other external data, the clinical research associate will perform 100% of the source data verification.

Statistical analysis

A statistical analysis plan (SAP) will be written on the basis of the study protocol. The SAP will provide further detailed descriptions of the statistical analysis content and methods.

The statistical analysis datasets will include the full analysis set (FAS), the per-protocol set (PPS), and the safety set (SS). All statistical tests will be conducted as two-sided tests. Descriptive statistics, such as the mean, median, standard deviation, maximum, minimum, Q1, and Q3, will be used to summarize the data. All statistical analyses will be performed via SAS version 9.4 or above to ensure the accuracy and reliability of the results. Missing items in study scales will be primarily addressed using mixed-effects model repeated measures (MMRM), observed case (OC), or last observation carried forward (LOCF) imputation methods.

The overall statistical analysis will include participant distribution, demographic and baseline characteristics, efficacy analysis, and safety analysis. With respect to participant distribution, we will summarize the number of screened participants, those randomized into the study, and those who completed the trial. Additionally, we will conduct in-depth analyses of dropouts and their reasons for discontinuation. Treatment compliance will be assessed by pill counts and patient diary using the formula: Compliance (%) = (actual dose (tablets)/theoretical dose (tablets)) × 100.

In terms of demographic and baseline characteristics, descriptive statistics will be used to summarize relevant information about the participants in each group, including their past treatment history. For efficacy analysis, the change in HAMD-17 score at week 8 relative to baseline for the primary efficacy indicator will be statistically analyzed via MMRM and analysis of covariance (ANCOVA). All secondary efficacy indicators will be analyzed via a group t-test. For safety analysis, the Medical Dictionary for Regulatory Activities (MedDRA) will be used to code adverse events, and the number of cases, number of participants, and incidences of all adverse events, adverse events related to the test drug, and serious adverse events will be calculated separately for each group. Additionally, clinical judgement results for laboratory test outcomes before and after treatment will be summarized via contingency tables.

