**Figure 1 FIG1:**
[figure not shown]
Flowchart of the study HAMD-17: 17-item Hamilton Rating Scale for Depression

Basic Study Period (Weeks 0-8)

A multicentre, randomized, double-blind, placebo-controlled parallel design will be employed. During the basic study period, a stratified and block randomization method will be used. All participants will be randomly assigned at a 1:1 ratio to either the experimental group (Shuganjieyu capsules combined with fluoxetine) or the control group (Shuganjieyu capsule simulant combined with fluoxetine). The evaluation during the basic study period will be conducted via double-blind and single-simulation techniques; i.e., both the investigator and the participants will be required to remain “blinded” during the grouping and evaluation. Additionally, the preparation of the placebo used in the control group will ensure that it matches the experimental drug in sensory aspects (such as dosage form, shape, colour, texture, and odour). The placebo will not contain the active ingredients of the experimental drug. This design will minimize subjective errors and ensure the objectivity and reliability of the trial results.

Extended Study Period (Weeks 9-24)

A multicentre, open-label observational study will be conducted. After completing the 8-week treatment period in the basic study period, the investigator will adjust the dosing regimen according to the condition of the participants, either to continue maintaining the treatment regimen of the basic study period in the experimental/control group or to adjust the dosing regimen for the experimental group. The design of the extended study period aims to align with clinical practice.

Sample Size Calculation and Randomization and Blinding Methods

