This study will be a superiority trial randomized 1:1 to the experimental group (Shuganjieyu capsules combined with fluoxetine) and the control group (Shuganjieyu capsule simulant combined with fluoxetine). The sample size will be calculated based on the following assumptions: the relative baseline change in the HAMD-17 score at 8 weeks is expected to be -13.3 for Shuganjieyu capsules combined with fluoxetine and -11 for the Shuganjieyu capsule simulant combined with fluoxetine. The difference in score reduction (δ) will be -2.3, the standard deviation (SD) will be 4.3, the two-sided type I error will be set at 0.05, and the statistical power will be 85%. Given a 20% dropout rate, each group will require 80 participants, resulting in a total of 160 participants.

In the basic study period of this trial, a stratified block randomization method will be adopted, with the study center as the stratification factor. Block randomization will be conducted within each center. The randomization list will be generated by the randomization statistician using SAS 9.4 statistical software (SAS Institute, Cary, USA) based on stratification factors and grouping ratios. Confidential parameters, including the number of blocks, block length, and random seed values, will be sealed in opaque envelopes along with the randomization list as the allocation schedule, which remains unopened during the trial. After completing the 8-week basic study period observation, investigators at each center will unblind the drug coding for individual patients.

Participant Selection

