Each clinical trial centre will perform unblinding only for participants who meet the specified criteria. Participants who do not complete the 8-week visit during the basic study period will remain blinded. Once all participants’ 24-week CRF data are fully entered and after any queries are addressed and no outstanding issues are observed, the data will be locked for final analysis.

Efficacy and safety indicators

Efficacy Indicators

The efficacy assessment indicators will include the following: (1) the primary efficacy endpoint will be the change in the HAMD-17; (2) the secondary efficacy endpoint will include the change in the Hamilton Anxiety Rating Scale (HAMA), Clinical Global Impression (CGI), Patient Health Questionnaire-15 (PHQ-15), Pittsburgh Sleep Quality Index (PSQI), Dimensional Anhedonia Rating Scale (DARS), Temporal Experience of Pleasure Scale (TEPS), and Quality of Life Enjoyment and Satisfaction Questionnaire-Short Form (Q-LES-Q-SF); the rate of patients with dose adjustments during the basic study period (8 weeks); the rate of relapse of depression symptoms at 12, 16, and 24 weeks of treatment in subjects who achieve clinical recovery/remission at 8 weeks of treatment; and the rate of medication changes/additions in participants who complete 8 weeks of treatment and enter the extended study period.

In this context, relapse will be defined as the recurrence of symptoms after achieving partial relief (effective, HAMD-17 reduction rate ≥ 50%) or clinical remission (complete symptom disappearance, HAMD-17 score ≤ 7) after the acute period of treatment [21].

Safety Indicators

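### Code breaks by centre investigators at each participant's week 8 can reveal the arms of block-mates still awaiting the primary HAMD-17 rating

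*Protocol article*

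**What the plan says.** All references are to the protocol article.

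- **Blinding.** Basic Study Period (Weeks 0-8): "A multicentre, randomized, double-blind, placebo-controlled parallel design will be employed", and "both the investigator and the participants will be required to remain “blinded” during the grouping and evaluation". The section relies on this for the objectivity of the results.
- **Randomisation.** Sample Size Calculation and Randomization and Blinding Methods: "This study will be a superiority trial randomized 1:1 to the experimental group" or to control, stratified by centre; "Block randomization will be conducted within each center".
- **Safeguard.** Same section: "Confidential parameters, including the number of blocks, block length, and random seed values, will be sealed in opaque envelopes along with the randomization list", and the envelopes stay unopened during the trial.
- **Code break.** Same section: "After completing the 8-week basic study period observation, investigators at each center will unblind the drug coding for individual patients". Dosage Regimen repeats that centre investigators open individual codes once the 8 weeks are complete and the CRF data are entered. It adds that unblinding is limited to participants who meet the criteria, and that those without a week-8 visit stay blinded.
- **Lock.** Dosage Regimen: only when everyone's 24-week data are in and queries are settled, "the data will be locked for final analysis".
- **Primary endpoint.** Statistical analysis: change in HAMD-17 from baseline to week 8. Quality control says that the primary efficacy assessment rests on scale evaluations.

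**The concern.** The group required to be blind during allocation and evaluation is also the group that opens codes, one participant at a time, while the same centre may still be enrolling and rating. In a 1:1 block, each revealed arm shifts the odds for the remaining members, and once one arm is used up the rest are certain. HAMD-17 is scored by judgement, so a rater who knows or can guess the arm may score differently without intending to. The same knowledge weakens concealment of the next assignments in the centre.

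A second route does not depend on block length. The week-8 record must be entered before the code is opened, but nothing in the article says it is closed. The primary value can therefore be queried and changed when the arm is already known. Neither kind of bias can be removed in the analysis afterwards.

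**Working it through.** **1. The plan's own sample size reproduces.** With δ = 2.3, SD = 4.3, two-sided α = 0.05 and power 85%, the normal formula gives 2 × (1.960 + 1.036)² × 4.3² / 2.3² = 62.8, so 63 per group. The t-test version gives 63.7, so 64, and 64 / 0.8 = 80. This point changes no sample-size figure. The expected number of evaluable participants is 160 × 0.8 = 128.

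**2. Is unblinding rolling, or a single event?** The code-break sentence read alone could mean one unblinding at the end of the basic period. It does not fit the rest. For participants with less than a 50% reduction, extension treatment differs by arm (Dosage Regimen), and the next visit after week 8 is week 12 (Table 1). The arm must therefore be known at about each participant's own week 8.

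**3. When does this reach a later participant?** Visits have a ±3-day window, so two week-8 visits can move 3 + 3 = 6 days relative to each other. A block-mate who enters more than 6 days, plus CRF entry time, after an earlier completer is rated after that completer's code can be opened. Prediction of assignments not yet made needs recruitment at the centre to run beyond about 8 weeks. The article gives no recruitment period or number of centres, so staggered entry is an assumption.

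**4. Share of allocations certain.** Take a block of 2m with known length and boundaries, and all earlier completers' codes open. A participant's arm is certain when all m members of the other arm came earlier and are revealed.

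- No dropout: share certain = 1/(m+1).
- Each participant revealed with probability 0.8: share certain = 0.8^m/(m+1).

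**5. Chance that the best guess is right.** Without dropout, the expected number of correct guesses per block is m + (4^m/C(2m,m) − 1)/2. For m = 2 this is 2 + (16/6 − 1)/2 = 2.833, and 2.833/4 = 0.708. For m = 3 it is 4.1, and 4.1/6 = 0.683. For m = 4 it is 4 + (256/70 − 1)/2 = 5.329, and 5.329/8 = 0.666. With dropout the figures come from simulation (6,000 blocks per setting, staggered entry, ±3-day windows, code opened directly after week 8).

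| Assumed block length | Certain, no dropout | Best guess right | Certain, 20% never unblinded | Best guess right |
|---|---|---|---|---|
| 4 | 1/3 = 33% | 71% | 0.64/3 = 21% | 66% |
| 6 | 1/4 = 25% | 68% | 0.512/4 = 13% | 63% |
| 8 | 1/5 = 20% | 67% | 0.4096/5 = 8% | 62% |

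The simulated shares certain with dropout (0.21 to 0.22, 0.13 and 0.08) agree with the formula. A blinded rater would be right 50% of the time. Of 128 completers, the dropout column means about 128 × 0.213 = 27, 128 × 0.128 = 16 or 128 × 0.082 = 10 ratings made with the arm deducible.

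**6. What a rating bias would do (illustration only).** With 64 per arm, SE = 4.3 × √(2/64) = 0.760. Under no true effect, an assumed mean between-arm bias of 0.5 points raises the two-sided type I error from 5% to about 10%; 1.0 point raises it to about 26%. If bias came only from the certain allocations at length 4 with dropout, a mean of 0.5 would need a gap of 0.5/0.213 = 2.3 points among those ratings. These show sensitivity and do not estimate the bias.

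**The case against.** The strongest reply is that the percentages describe an event the plan guards against. Length, number of blocks, seeds and list are sealed, and a rater would need length, boundaries and an ordered record of codes. This stands as far as the size goes: every figure in the table is conditional. It does not remove the risk, because codes revealed in sequence within a centre carry information even when the envelope stays shut.

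Other points that stand:

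- Not every earlier block-mate will have been unblinded. The visit windows, CRF entry before the code break, week-8 non-completers, and possibly completers who do not enter the extension all reduce what is known.
- Codes are opened only after data entry, and the EDC audit trail and source data verification make later edits traceable. They do not prevent them.
- A journal article may leave rater roles to the full protocol or SOPs. If separate blinded raters are named there, much of the rating concern falls away. Even so, this article assigns code breaking to the same role that it requires to be blind.

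A reader might infer that the block length is fixed, because the term appears in the singular. It stands in a list of confidential parameter types, and varying lengths may already be in use. A reader might also infer that the person opening a code is the one rating HAMD-17, or that week-8 ratings are in fact biased. The article states neither and gives no basis for estimating a bias.

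**Conclusion.** The concern holds as a conflict within the article and a conditional risk to the primary endpoint. Code breaking by centre investigators at each participant's week 8, combined with 1:1 blocks within centre, cannot be squared with keeping the investigator blind during allocation and evaluation unless roles are separated, and no separation is described.

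Using the plan's own 20% dropout, 8% to 21% of week-8 ratings would be made with the arm certain for block lengths 8 to 4; without dropout, 20% to 33%. These figures assume staggered enrolment, known block length and boundaries, and prompt opening of earlier codes. With slower code release or fewer codes opened they fall. The absence of a stated freeze on week-8 records before the code break is a separate weakness and needs none of these assumptions. The documents do not support a claim that the trial is unblinded or that its result will be biased.

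**What to change.** The article says that the trial is ongoing, so participants not yet rated can still be protected.

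1. **Separate the roles.** Release code-break results only to the drug administrator and the extension prescriber. Have HAMD-17 in weeks 0-8 rated by already-trained site staff without access to those codes. These raters should also not run extension visits while the centre has participants in weeks 0-8, because the open-label regimen can show the arm. If the full protocol or SOPs already provide this, say so.
2. **Freeze before release.** Resolve queries and freeze a participant's weeks 0-8 eCRF pages in the EDC before that participant's code is released.
3. **Pre-specify a sensitivity analysis.** Repeat the primary analysis excluding participants whose allocation was deducible from earlier code breaks at their week-8 visit, using the list and logged code-break dates. It will not capture guesses that are better than chance but short of certain, so it supplements steps 1 and 2 and does not replace them.

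Varying block lengths should be considered only if not already used, and only where unallocated coded supplies allow it. Blinded drug is delivered to centres, so changing the list may mean re-coding supplies.

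The cost is a short protocol or SOP amendment, an EDC freeze step, one extra analysis and a slight administrative delay before each code release. Sample size, treatment and visits do not change.

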These criteria will standardize the study process, ensure its rigor, and protect the rights and interests of participants from an ethical perspective. The inclusion criteria for participants in this study will include the following: (1) meeting the diagnostic criteria for depression according to the Diagnostic and Statistical Manual of Mental Disorders (5th edition) (DSM-5); (2) aged 18-65 years (inclusive), regardless of sex; (3) HAMD-17 score ≥ 18 in the screening period, and Item 13 score ≥ 2; (4) negative pregnancy test; and (5) voluntary signing of the informed consent form and agreement to participate in all visits, examinations, and treatments according to the trial protocol. The exclusion criteria will include the following: (1) treatment-resistant depression (lack of clinical efficacy after adequate treatment with two or more different mechanisms of antidepressant drugs), depression caused by psychotropic drugs, depressive secondary to other mental illnesses, or somatic diseases at an active stage; (2) individuals meeting DSM-5 criteria for other mental disorders (such as schizophrenia spectrum and other psychotic disorders, bipolar and related disorders, anxiety disorders, obsessive-compulsive and related disorders, somatic symptoms and related disorders); (3) severe suicidal tendencies (HAMD-17 suicide score ≥ 3) or a tendency to harm others; (4) severe or unstable cardiovascular, cerebrovascular, liver, kidney, endocrine, digestive and blood diseases; liver function tests showing alanine aminotransferase (ALT), aspartate aminotransferase (AST) > 2 times the upper reference limit, or serum creatinine (SCr) > upper reference limit; patients with a history of hyperthyroidism, hypothyroidism, or other endocrine diseases currently in an active period; (5) patients who have undergone psychiatric surgery or electroconvulsive therapy in the past 3 months; those who have not responded to previous treatment with Shuganjieyu capsules or fluoxetine; those who have received or are currently receiving any other investigational drug therapy within 3 months before the trial; patients taking interfering drugs contraindicated with the investigational drug, or those who have received systemic antidepressant therapy within 4 weeks; patients with psychoactive substance abuse or dependence in the past 12 months; (6) patients with known or suspected allergies to *Hypericum perforatum*, *Eleutherococcus senticosus*, or fluoxetine; long-term use of caffeine and nicotine; and (7) other individuals who are deemed unsuitable for participation in this clinical trial by the researchers.

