During the basic study, the experimental group will receive oral fluoxetine (20 mg/dose, once daily) with Shuganjieyu capsules (two capsules/dose, twice daily, morning and evening). The control group will receive fluoxetine (20 mg/dose, once daily) with Shuganjieyu capsule simulant (two capsules/dose, twice daily, morning and evening). If the HAMD-17 total score reduction rate is less than 20% at the end of the second week, the dosage of Shuganjieyu capsule or simulant will be adjusted to four capsules/dose, twice daily, in the morning and in the evening.

After completing the 8-week basic study period and entering case report form (CRF) data, the investigators at each centre will unblind the drug codes corresponding to individual participants. On the basis of the participants’ condition after 8 weeks of the basic study period, an extended study period medication plan was formulated. For participants who enter the extended study period, if their HAMD-17 total score reduction rate is less than 50%, the fluoxetine dosage will be adjusted to 40 mg/dose once daily for the experimental group. For the control group, Shuganjieyu capsules (two capsules/dose, twice daily, morning and evening) will be added first, and further adjustments to the fluoxetine dosage (40 mg/dose, once daily) will be considered on the basis of changes in the participant’s condition. Participants will be prohibited from concurrently using other antidepressant medications during both the basic and extended study periods. During the basic study period, the use of other auxiliary treatments for depression will be prohibited, such as psychotherapeutic intervention and rehabilitation therapy, modified electroconvulsive therapy, transcranial magnetic stimulation, vagus nerve stimulation, deep brain stimulation, and other physical therapies. During the extended study period, the use of other auxiliary treatments for depression will be prohibited, including modified electroconvulsive therapy, transcranial magnetic stimulation, vagus nerve stimulation, and deep brain stimulation, but psychological interventions will be permitted.

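### The relapse endpoint has two different populations, and comparing arms within either is not a randomised comparison that can by itself support the relapse-prevention aim

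*Protocol article*

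**What the plan says.** All places are in the protocol article.

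- **Efficacy Indicators, endpoint list.** The secondary efficacy endpoints include "the rate of relapse of depression symptoms at 12, 16, and 24 weeks of treatment in subjects who achieve clinical recovery/remission at 8 weeks". Recovery is not defined separately.
- **Efficacy Indicators, next paragraph.** For this endpoint, "relapse will be defined as the recurrence of symptoms after achieving partial relief (effective, HAMD-17 reduction rate ≥ 50%) or clinical remission". The second starting state is specified as "clinical remission (complete symptom disappearance, HAMD-17 score ≤ 7".
- **Participant Selection.** Entry requires "HAMD-17 score ≥ 18 in the screening period, and Item 13 score ≥ 2".
- **Dosage Regimen.** Once the eight-week period is complete and its data are entered, "the investigators at each centre will unblind the drug codes corresponding to individual participants". In the later period other physical treatments stay prohibited, "but psychological interventions will be permitted".
- **Extended Study Period (Weeks 9-24).** "A multicentre, open-label observational study will be conducted". No second randomisation is described.
- **Statistical analysis.** All secondary efficacy indicators are assigned a group t-test.
- **Discussion.** Assessing efficacy in preventing relapse over the continuation phase is stated as an aim. The abstract's discussion uses the softer language of exploring long-term efficacy.

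**The concern.** Two things are at issue.

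First, the endpoint sentence and the definition that serves it start from different groups. One analyst could take week-8 remitters as the denominator and another could take everyone with at least a 50% reduction. Both would be following the text. Unless this is settled beforehand, the choice could be made with the data in view.

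Second, whichever group is used, membership is decided at week 8 by an outcome that the trial expects treatment to change. If the planned effect is real, the experimental subset includes people who would not have reached that state on control. The subsets are then no longer the randomised groups, and a difference in later relapse mixes any drug effect with a difference in who was selected. Follow-up is also open-label, with psychological interventions allowed. A t-test between arms on this rate, read alongside the Discussion's aim, would be taken as evidence of efficacy that the design does not provide.

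**Working it through.** **1. The plan's own figure.** Inputs from the sample size section: expected changes −13.3 and −11, difference 2.3, SD 4.3, two-sided 0.05, power 85%, dropout 20%.

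n per arm = 2 × (1.960 + 1.036)² × 4.3² / 2.3² = 62.8, so 63. The exact t calculation gives 64, and 64 / 0.8 = 80, as stated. The sample size reproduces and is not in dispute. It concerns the week-8 HAMD-17 change only; no size is stated for the relapse endpoint.

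**2. How the two populations relate.** The smallest entry score is 18. Reaching 7 from 18 is a reduction of (18 − 7) / 18 = 61.1%, and the percentage is larger from any higher start. Every remitter is therefore a responder. The reverse fails: going from 18 to 9 is a 50% reduction without remission. Remitters are a strict subset.

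**3. Size of each population.** The documents give no baseline mean, so I assume a common baseline b of 20, 22 or 24, a normally distributed change with the plan's means and SD, and 64 completers per arm (80 × 0.8). With m the expected reduction (11 or 13.3):

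- P(response) = 1 − Φ((b/2 − m) / 4.3)
- P(remission) = 1 − Φ((b − 7 − m) / 4.3)

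For b = 22, control: response 1 − Φ(0) = 0.500, remission 1 − Φ(4/4.3) = 0.176. Experimental: 1 − Φ(−2.3/4.3) = 0.704 and 1 − Φ(1.7/4.3) = 0.346. Multiplying by 64:

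| Assumed baseline | Remitters, control | Remitters, experimental | Responders, control | Responders, experimental |
|---|---|---|---|---|
| 20 | 20.5 | 33.8 | 37.9 | 49.8 |
| 22 | 11.3 | 22.2 | 32.0 | 45.0 |
| 24 | 5.2 | 12.5 | 26.1 | 39.6 |

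Depending on which sentence is followed, the control denominator changes by a factor of 1.8 (37.9/20.5) to 5.0 (26.1/5.2). At every baseline a larger share of the experimental arm is selected.

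**4. How far selection alone could move the relapse rate.** This is an illustration, not an estimate. A prognostic factor U (standard normal, higher is better) has correlation r with the week-8 improvement. Relapse has logit −1.2 − 0.9U in both arms, so there is no drug effect after week 8. The intercept, slope and r are assumptions. At baseline 22, with 2 million draws:

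| r | Remitters, experimental vs control | Gap (points) | Responders, experimental vs control | Gap (points) |
|---|---|---|---|---|
| 0 | 26.3% vs 26.3% | 0 | 26.3% vs 26.3% | 0 |
| 0.3 | 21.5% vs 19.9% | 1.6 | 24.0% vs 22.6% | 1.4 |
| 0.5 | 18.4% vs 16.0% | 2.4 | 22.4% vs 20.2% | 2.2 |
| 0.7 | 15.4% vs 12.5% | 2.9 | 20.7% vs 17.7% | 3.0 |

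For scale, the standard error of the difference at r = 0.5 with 22 and 11 remitters is √(0.184 × 0.816 / 22 + 0.160 × 0.840 / 11) = 0.138, or about 14 points.

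**5. What an all-randomised composite would show in the same model.** At b = 22 and r = 0.5, remission at week 8 without later relapse is 0.346 × (1 − 0.184) = 28.2% versus 0.176 × (1 − 0.160) = 14.8% of completers. If the planned 20% dropout is counted as failure (assumed unrelated to outcome, with no further loss), these become 22.6% and 11.8% of those randomised. The comparison respects randomisation. But the model has no drug effect after week 8, so the whole gap is the week-8 effect carried forward.

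**The case against.** The best defence is that the endpoint sentence says who is counted and the next paragraph only explains the term. A definition covering responders can be applied to remitters without contradiction, and the undefined word recovery may have been meant to cover the wider group. This shows that a harmless reading exists. It does not show which reading is intended, because the definition is introduced for this very endpoint and names a different starting state.

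The second defence is that the protocol openly calls weeks 9–24 observational, speaks of exploring long-term efficacy, and nowhere states a test of relapse between arms. This stands in part: a descriptive rate per arm is unobjectionable. But the t-test is assigned to all secondary indicators, relapse is one of them, and the Discussion words the aim as efficacy in preventing relapse.

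Third, the selection bias is small. That stands. In the illustration it is about one-sixth of the standard error (2.4 / 13.8), and it depends on assumed inputs.

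Several stronger readings are tempting but not supported:

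- **That the relapse event lacks a score criterion by oversight.** The article gives none, but the definition cites a source, and an analysis plan is announced. The criterion may sit in either.
- **That relapse is the trial's main long-term claim.** It is one of several secondary indicators.
- **That treatment switching at week 8 removes the contrast between arms.** Under Study design, control participants with more than a 50% reduction continue on fluoxetine alone, so the contrast persists among those responders. The difficulty is selection and open-label follow-up.

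**Conclusion.** The point holds for a secondary endpoint. The document gives it two nested populations that differ materially in size: at an assumed baseline of 22, about 11 versus 22 remitters or 32 versus 45 responders (control versus experimental). The implied arm comparison is made in a subset selected after randomisation and followed after unblinding, so it cannot by itself support an efficacy claim about preventing relapse.

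That the populations are nested follows from the entry and remission thresholds alone. The counts rest on the plan's expected changes and SD, a normal model, 64 completers per arm and an assumed baseline. The bias of roughly 2–3 points against the better arm (r of 0.5–0.7; about 1.5 at 0.3; none at zero) rests on assumed prognostic inputs.

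A reader might infer that the better arm would be seriously penalised; these figures do not show that. Bias from open-label assessment is a separate matter, and the documents give no basis for sizing it.

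**What to change.** 1. Reconcile the two sentences under Efficacy Indicators to one denominator, or report remitters and responders separately. State what recovery means.
2. Base the relapse event on the HAMD-17 scores already scheduled at weeks 12, 16 (by telephone) and 24, using one criterion fixed before data lock. If the analysis plan already holds such a criterion, refer to it.
3. Report the conditional relapse rate by arm as descriptive.
4. Make the between-arm comparison the proportion of all randomised participants who are in remission at week 8 and relapse-free to week 24. Analyse it as a proportion instead of by t-test, count missing as failure, and add a sensitivity analysis for missing data.
5. Soften the relapse-prevention wording in the Discussion to match.

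The cost is revised endpoint text and one derived variable from data already being collected. The article describes the trial as ongoing, with lock after the 24-week data, so there is room to do this beforehand. There are downsides. The composite mixes the week-8 remission effect with later relapse, so it shows sustained benefit and not relapse prevention alone. Assessment after week 8 remains open-label. The conditional rate loses its standing as a test between arms.
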